**Record retention and archiving**

Data will be retained and archived in accordance with the UK Policy Framework for Health and Social Care Research, East London NHS Foundation Trust Record Management and IM&T Information and security policies. All essential documents will be archived for 20 years after completion of trial and stored in the Trust Modern Records Centre. The Chief Investigators will be the custodian of the data. Participants’ contact details will be retained (with their permission via the consent form) if they want to be updated about the study progress. These will then be destroyed 1 year after the study end.

### Confidentiality {27}

The trial will be compliant with the requirements of the Data Protection Act, 2018, with regard to the collection, storage, processing and disclosure of personal information and will uphold the Act’s core principles, throughout the study.

**Personal information**

All data will be pseudonymised to maintain patient confidentiality. All participants will be assigned participant ID number used for all data processing purposes and the list linking these data with the participant ID number will be stored on NHS computers on a secure drive, within password-protected folders, which will only be accessible to the research team. All hard copies of data, including signed consent forms, socio-demographic details and patient receipts, will be kept and locked securely and separately from pseudonymised data and only accessible by the research team. Where participants provide their consent, participant’s names and contact details will be retained to enable the research team to re-approach them to take part in related studies and to share research findings.

**Pseudonymised data**

Pseudonymised CRF data will be stored in a locked filing cabinet at each site, kept separate from the anonymisation code sheet identifying participants. Data will be entered into a web-based database developed by the PCTU Data Management team. All data stored on the database will be pseudonymised by using the participant ID as the identifier. The database will be accessed by researchers working on the study.

**Audio visual recordings**

Audio-visual recordings of all therapy sessions (arts therapies and group counselling) and individual interviews will be taken with explicit permission (as indicated on the consent form) from participants. Recordings will be stored on password-protected folders on NHS Trust computers on a secure drive which will only be accessible by the research team. Audio recordings of interviews will be destroyed immediately after transcription and the transcriptions will not contain any identifiable information. Audio-visual recordings will be destroyed 1 year after the trial as finished, with only excerpts of sessions kept for presentation purposes. These excerpts will not contain any identifiable images or sounds of participants and will be used only with the explicit consent of participants (as outlined in the information sheet and consent form).

**Access to data**

Access to pseudonymised data will be limited to the following personnel who may all be involved in handling or analysing data during the study: the trial manager, CIs, service user lead, research assistants, clinical studies officers and PCTU staff. No identifying data will be sent to the sponsor or TSC/DMEC members. The only occasion where information on patients may need to be transmitted via NHS email or telephone would be in the case of a serious adverse event, where a therapist may need to contact the CI. In this case, Trust guidelines will apply, i.e. minimally identifying data will be used on the emails, NHS to NHS email only will be used and NHS guidelines for checking caller identities for phone calls will be followed.

### Plans for collection, laboratory evaluation and storage of biological specimens for genetic or molecular analysis in this trial/future use {33}

Not applicable as no biological specimens are being collected.

## Statistical methods

### Statistical methods for primary and secondary outcomes {20a}

A detailed statistical analysis plan will be drafted by the trial statisticians and signed off by the independent statistician on the Trial Steering Committee prior to the analysis of unblinded data.

Baseline data

We will report descriptive statistics for sociodemographic and clinical characteristics by intervention arm along with baseline scores for each assessment.

**Primary outcome analysis**

The primary analysis will be a longitudinal mixed regression analysis that includes end of treatment, 6-month post-treatment and 12-month post-treatment assessments of psychological distress, using all non-missing data on these outcomes. Performing a longitudinal analysis of all time-points using all non-missing data should allow for greater precision in the estimation of treatment effect at end of treatment than an analysis of this time-point alone. However, to allow results on the primary outcome to be reported in a timely fashion, we will also conduct and report an initial analysis of the first two time-points—baseline and end of treatment—as soon as these are available for all participants. The analysis will include random effects to allow for clustering within each therapy group and individual. The primary hypothesis of a beneficial effect of arts therapy will be investigated by testing for a fixed effect of intervention vs. control, adjusting for fixed effects of site, patients’ preference for the form of arts therapy (art, music or dance), primary diagnosis, age, sex and baseline psychological distress. The primary analysis will be by intention to treat. Secondary analyses will investigate the treatment effect in compliers.

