## Trial design {8}

A pragmatic, two-arm randomised controlled superiority trial comparing group arts therapy (art, dance movement, music) to an active group counselling control, with economic evaluation and nested process evaluation. Participants will be randomised in batches, each batch sufficient in size to populate two therapy groups within a given preference stratum at a site. Randomisation will be 1:1 unless a batch has fewer than 15 participants, in which case a 2:1 allocation ratio of intervention to control will be applied.

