## Assignment of interventions: allocation

### Sequence generation {16a}

Randomisation will be on a site-by-site basis (three sites in the first phase of recruitment, and four sites in the second stage) and will be further stratified at each site by preferred modality. To minimise the time between enrolment and commencing the intervention, we will aim to conduct randomisation as soon as a batch of 20 people with the same modality preference have been enrolled at a site and have completed baseline measures. Participants in each batch of 20 will be randomised in a 1:1 ratio to two therapy groups, one receiving the preferred modality and one receiving group counselling (the control), using constrained randomisation to balance the distribution of primary diagnosis, age and gender in each therapy group. We implement constrained randomisation using the cvrand command in Stata [42].

If 15–19 participants with a preferred modality are still to be randomised at the end of the recruitment window, they will be randomised 1:1 to two therapy groups, with the possibility to add non-study participants to maintain numbers within the group. In the case where there are fewer than 15 participants with a preferred modality at the end of the recruitment window, they will be randomised (where feasible) in a 2:1 ratio to intervention and control, with the option of enlarging groups with non-study patients.

At the end of recruitment, there is a chance that the number of participants with a preferred modality is below that of the number required to feasibly run a group. Taking into account drop-out and non-attendance, we estimate that we require a minimum of 8 participants for a group to be viable. This equates to a minimum of 12 participants in a randomisation batch if randomising 2:1. In order to minimise the loss of already consented participants, we will ask participants to provide a second modality choice and also to indicate whether or not they would be willing to receive this in case numbers for their original preferred modality cannot be met.

Where the number in a preference stratum at the end of recruitment is fewer than 12, we will consider enriching this stratum with participants for whom the modality was their second choice, to give a sufficient number to be randomised as a batch. If a participant is unwilling to receive a second choice, we will withdraw them from the study and signpost them to local services.

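### The primary model leaves out the randomisation batch, although patients are randomised batch by batch at a ratio that can change from 1:1 to 2:1; the consequences are modest and the remedy is one model term

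*Protocol article*

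**What the plan says.** Under Trial design {8}, the unit of randomisation is the batch: "Participants will be randomised in batches, each batch sufficient in size to populate two therapy groups within a given preference stratum at a site". The ratio depends on batch size: "Randomisation will be 1:1 unless a batch has fewer than 15 participants, in which case a 2:1 allocation ratio of intervention to control" applies.

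Sequence generation {16a} gives the detail. The standard case is "Participants in each batch of 20 will be randomised in a 1:1 ratio to two therapy groups", one for the preferred arts therapy and one for counselling. The 2:1 rule is tied to timing: with "fewer than 15 participants with a preferred modality at the end of the recruitment window, they will be randomised (where feasible) in a 2:1 ratio". The smallest such batch follows from a viable group of 8: "This equates to a minimum of 12 participants in a randomisation batch if randomising 2:1", that is 8 + 4. Below 12, the plan states that "we will consider enriching this stratum with participants for whom the modality was their second choice".

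Primary outcome analysis then names the terms of the model. For clustering: "The analysis will include random effects to allow for clustering within each therapy group and individual". The fixed effects are arm, site, preferred art form, primary diagnosis, age, sex and baseline distress. Neither list contains batch, a site-by-preference term, calendar period or allocation ratio. Secondary outcome analysis applies the same model to all secondary outcomes.

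**The concern.** A site-by-modality stratum can hold several batches over time, some at 1:1 and a last one at 2:1. Main effects of site and preference therefore do not identify the ratio that a patient faced. The probability of receiving arts therapy is 1/2 in some batches and 2/3 in others, so patients of 2:1 batches make up a larger part of the arts arm than of the counselling arm. If their outcomes differ for reasons other than treatment (end of window, a less popular modality, second-choice participants), part of that difference enters the treatment estimate.

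Separately, the two groups of a batch share site, period and preference. Variation common to both cancels in their comparison, but the planned model counts it as independent noise in each group. What is at stake is a small possible bias and some lost precision in the primary and all secondary comparisons.

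**Working it through.** **Inputs from the document.** Sample size {14}: target effect 0.5 SD, SD of GSI 0.81, planning ICC 0.1, ICC not above 0.01 in the earlier group body psychotherapy trial, 10 allocated and 8.5 analysed per group, coefficient of variation 0.5, and 2 × 210 patients. Sequence generation {16a}: batches of 10 + 10, and of 8 + 4 at the smallest 2:1 size.

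**Assumptions, because the document gives no figure.** The share of the ICC common to both groups of a batch (0 to 75%), the number of 2:1 batches (3 or 7 of 21), and the residual outcome shift of 2:1 batches (0.3 to 0.5 SD).

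**The plan's own figure.** Without clustering, 2(1.96 + 1.2816)²/0.5² = 84.06, taken as 85 per arm. Design effect = 1 + ((1 + 0.5²) × 8.5 − 1) × 0.1 = 1.9625. Then 85 × 1.9625 = 166.8 analysed, 166.8/8.5 = 19.6 groups, hence 20 groups and 200 allocated per arm. The stated 200 is reproduced and this point does not touch it.

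**Bias from the varying ratio.** The planned model weights a group of n allocated patients by w(n) = 1/[ICC + (1 − ICC)/(0.85n)]. With k of 21 batches at 8 + 4 and the rest at 10 + 10, the weight carried by 2:1 batches is

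- arts arm: p_A = k·w(8)/[k·w(8) + (21 − k)·w(10)]
- counselling arm: p_C = k·w(4)/[k·w(4) + (21 − k)·w(10)]

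and bias = shift × (p_A − p_C). At ICC 0.1, w(10), w(8) and w(4) are 4.857, 4.304 and 2.742. At ICC 0.01 they are 7.907, 6.427 and 3.320.

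| ICC | k | p_A | p_C | Bias per 1 SD shift | Bias for shift of 0.3 to 0.5 SD |
|---|---|---|---|---|---|
| 0.1 | 3 | 0.129 | 0.086 | 0.043 | 0.013 to 0.021 |
| 0.1 | 7 | 0.307 | 0.220 | 0.087 | 0.026 to 0.043 |
| 0.01 | 3 | 0.119 | 0.065 | 0.054 | 0.016 to 0.027 |
| 0.01 | 7 | 0.289 | 0.174 | 0.115 | 0.035 to 0.058 |

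The range is about 0.01 to 0.06 SD, or 0.01 to 0.05 GSI points (× 0.81). With k = 0, p_A = p_C and the bias is zero. With batch as a fixed effect, comparisons are made within batch and the bias is zero for any k.

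**Standard error.** With 10 + 10 batches and a share s of the ICC common to the pair:

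reported SE / true SE = √{[ICC + (1 − ICC)/8.5] / [ICC(1 − s) + (1 − ICC)/8.5]}

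| s | ICC 0.1 | ICC 0.01 |
|---|---|---|
| 0 | 1.00 | 1.00 |
| 25% | √(0.2059/0.1809) = 1.07 | √(0.1265/0.1240) = 1.01 |
| 50% | √(0.2059/0.1559) = 1.15 | √(0.1265/0.1215) = 1.02 |
| 75% | √(0.2059/0.1309) = 1.25 | √(0.1265/0.1190) = 1.03 |

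At ICC 0.1, with 21 batches, the reported SE is √(2 × 0.2059/21) = 0.140 SD; at s = 50% the true SE is 0.122. From the SE error alone, the actual two-sided error rate 2[1 − Φ(1.96 × ratio)] falls to 0.037, 0.024 and 0.014 for s = 25, 50 and 75%. Mixing in 2:1 batches changes little: 15 batches of 10 + 10 with 9 of 8 + 4 give 13% instead of 15% at s = 50%.

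**Degrees of freedom.** 21 batches give 42 groups. Without batch: 42 − 2 = 40 between-group degrees of freedom, critical t 2.02. With fixed batch effects: 42 − 21 − 1 = 20, critical t 2.09, about 3% wider.

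**The case against.** The strongest reply is that the effect is small and mostly safe. The only empirical ICC in the document is 0.01 at most; 0.1 was chosen as a cautious planning value. At 0.01 the SE is overstated by only 1 to 3%, which the wider critical t of fixed batch effects roughly cancels. The SE error never makes the test liberal, and at ICC 0.1 with half of it shared, power for 0.5 SD under the planned model is still 0.968 (0.984 with batch). The bias needs both several 2:1 batches and a systematic shift left after adjustment for baseline GSI and the other covariates, and the document supports neither figure. All of this stands and limits the size of the point.

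It could also be said that an analysis plan not shown may add batch. That does not remove the point, because the article states both the random and the fixed effects of the primary model, and batch is in neither list.

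Three stronger readings are tempting but unsupported. A reader might infer that the omission inflates false positives through the standard error; the error goes the other way. A reader might count every end-of-window remainder under 15 as a 2:1 patient; the 2:1 rule applies only where feasible, remainders under 12 may or may not be topped up with second-choice participants, and those unwilling to switch are withdrawn. And a reader might see the 16-month pandemic halt as a confounder in itself; each batch supplies both arms, so a calendar shift causes no bias across 1:1 batches. The Discussion also reports that an amendment was sought to re-assess and re-randomise those caught by the pause.

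**Conclusion.** The point holds in a limited form: the stated model does not follow the unit within which patients are randomised. If batches differ after adjustment, the treatment effect may be biased by about 0.01 to 0.06 SD, at most roughly an eighth of the 0.5 SD target (0.06/0.5 = 0.12), in a direction that cannot be known in advance. The SE would be overstated by 1 to 3% at ICC 0.01 and by 7 to 25% at ICC 0.1. Both effects vanish if batches do not differ, and the bias also vanishes if every batch is 1:1. The mechanism follows from the document. The size rests on an assumed batch share, an assumed shift and an assumed number of 2:1 batches. The sample size is unaffected. It is worth correcting because the remedy is cheap and can be prespecified: Statistical methods {20a} places sign-off of the analysis plan before analysis of unblinded data.

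**What to change.** Add randomisation batch to the primary model and, by the same rule, to the secondary outcome models, with therapy group as a random effect nested in batch.

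- Preferred: batch as a fixed effect replacing the site and preference main effects. This removes the confounding with allocation ratio fully. The interaction of modality stratum with arm can stay for the subgroup analysis.
- Alternative: batch as a random effect, keeping site and preference and adding a fixed indicator for allocation ratio (1:1 or 2:1).

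The cost is one model term and a batch identifier in the analysis data set, which the batchwise randomisation files described under Implementation {16c} should be able to supply (the article does not say that it is stored). Fixed batch effects halve the between-group degrees of freedom, from about 40 to 20, which roughly cancels the precision gain if the ICC is near 0.01. A therapy group whose paired group is lost would then contribute nothing to the treatment comparison; Sample size {14} allows for the loss of one group per arm, so the analysis plan should say how this case is handled.

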**Secondary outcome analysis**

Secondary outcomes, which are all on continuous scales, will be analysed in the same way as the primary outcome.

**Economic evaluation**

Economic evaluation will be undertaken from the NHS and personal and social services perspective to assess the cost-effectiveness of group arts therapies compared to group counselling for psychiatric patients. The evaluation will include within-trial analyses over the intervention period and the 12-month post-intervention follow-up period.

We will estimate the cost of delivering group arts therapies (i.e. art therapy, dance movement therapy and music therapy) and control intervention (i.e. group counselling). Resource use associated with delivery of all interventions will be documented by the study team over the 5-month treatment period using inventory forms developed by the trial Health Economist. Data on patients’ use of health and social care services will be collected at baseline, end of treatment and 6 and 12 months after treatment by the trial researchers using an adapted CSRI [39]. Costs for each type of resource (or service) use will be calculated as a product of the quantity of resource (or service) use and its corresponding unit cost. Cost items will be summed together and presented at baseline and 12 months after intervention for each patient. The primary health outcome measure in the economic evaluation is patients’ self-reported outcomes on the EQ-5D-5L instrument [37]. We will convert the ED-5D-5L data to quality-adjusted life years (QALYs).

Cost-utility analysis will be conducted. We will calculate the incremental cost-effectiveness ratio (ICER) of the group arts therapies compared to group counselling and then check the point estimate against a cost-effectiveness threshold value of £20,000 to £30,000 per QALY [48]. We will also report the uncertainties around the point estimate. In addition to the primary analysis, a few sensitivity analyses will be conducted including to (1) undertake analysis using broader analytical perspective in the economic evaluation by including estimated costs from productivity lost; (2) run the primary analysis use intervention period alone or intervention period and 6-month period after intervention as the time horizon; (3) perform two scenario analyses using the ReQoL-20 [38] and BSI [26] as the alternative health outcome measures; (4) consider uncertainty in the intervention costs; (5) explore the pattern of missing values in costs and outcome data and then identify an appropriate method to manage missing values; and (6) estimate ICER for each form of art therapy in order to assess its cost-effectiveness compared to group counselling.

### Interim analyses {21b}

**Stop/go criteria**

As an interim assessment of feasibility, we will examine recruitment rates in the first 6 months, alongside group attendance rates and observer-rated therapist adherence to the manual, using pre-defined stop–go criteria (Table 2). We will aim to recruit 180 participants (60 at each initial site). In week 4 of the intervention phase, the stop–go criteria will be discussed by the Trial Management Group (TMG), Trial Steering Committee (TSC) and funder to decide whether or not to continue the trial. Recruitment will continue throughout this time period, with the aim of commencing the next round of groups as soon as possible after receiving this decision.

**Table 2 Tab2:** Stop–Go criteria after 6 months of recruitment

**Criterion**	**Green** Progress to end of trial as planned	**Amber** Discussion with TSC and funder about progression	**Red** Trial is stopped
Recruitment within 6 months	≥ 90% of recruitment target at each site	66–89% of recruitment target at each site	< 66% of recruitment target at each site
Attendance of at least one group session in the first 4 weeks of intervention	≥ 90% of sample attend at least 1 session	66–89% of sample attend at least 1 session	< 66 of sample attend at least 1 session
Attendance rates in the first 4 weeks of the intervention	≥ 90% attendance rate	66–89% attendance rate	< 66% attendance rate
Therapist adherence to manual using observer-rated videos from sessions taken from weeks 2 and 3 of the intervention	≥ 90% agreement with manual criteria	66–89% agreement with manual criteria	< 66% agreement with manual criteria

No interim analyses of primary or secondary outcomes are planned. The DMEC will review data on outcomes and adverse events as they accrue, summarised by trial arm, arts therapy modality, study site and diagnosis. Should significant safety concerns arise during the intervention phase, the CI in liaison with the sponsor, TSC and DMEC has ultimate authority to halt the study or withdraw individual participants should concerns arise during the study.

### Methods for additional analyses (e.g. subgroup analyses) {20b}

**Subgroup analyses**

We will repeat analyses within diagnostic subgroups and investigate whether different forms of arts therapy have different effects by including an interaction between modality preference stratum and intervention vs. control in our mixed regression model.

Qualitative assessments and nested process evaluation

We plan to conduct a process evaluation in line with recommendations by the Medical Research Council [49]. The logic model of our intervention (described in our manual development paper [28]) provides a theory of the intervention describing assumptions and contextual factors that might shape implementation and outcomes, hypothesised processes and mechanisms of impact and our intended outcomes. The aim is to better understand the processes of group arts therapy in comparison to group counselling controls in practice and possible implications. In particular:

To understand exactly how the intervention was delivered in practice (treatment fidelity analysis).Describe processes of attendance and hypothesised process factors of self-reported depression, group experiences and session appraisal over the course of the trial.Understand subjective experiences and attributions for change of the intervention from the perspective of patients and arts therapists.Compare reported quantitative and qualitative processes against the proposed logic model and to revise accordingly.

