## Objectives {7}

The primary objective is to test the effectiveness of manualised diagnostically heterogeneous group arts therapy on reducing psychological symptoms in patients receiving treatment in community mental health services as compared to an active control of group counselling (both intervention groups will be in addition to treatment as usual). Secondary objectives are to: Apply stop/go criteria half-way through data collection to ensure recruitment and therapist adherence to the intervention are sufficient to continue the trial.Test the effectiveness of group arts therapy on observer-rated symptoms, quality of life and objective social situation (secondary outcomes).Test whether effects on primary and secondary outcomes hold true at 6- and 12-month follow-up periods post-intervention.Explore the impact of adherence (completers vs. non-completers, adherence of therapists to the manual), diagnosis and type of arts therapy upon outcomes in sub-group analyses.Explore processes in the above sub-groups in a nested process evaluation utilising treatment fidelity analysis, attendance data, measures of patient appraisal and experiences in the groups, and qualitative interviews exploring subjective experiences and attributions for change from the perspective of patients and therapists.Assess the cost-effectiveness of group arts therapies in an economic evaluation alongside the trial.

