### Sample size {14}

We have designed the trial to detect a treatment effect of 0.5 standard deviations on the primary health outcome, i.e. the level of psychological distress, as measured by the Brief Symptom Inventory Global Severity Index. In a sample of 378 patients from a UK psychiatric outpatient population, the mean GSI was 1.65 with a standard deviation of 0.81 [40]. An effect of 0.5 standard deviations would therefore represent a difference of 0.4 on the GSI. We assume clustering of outcomes of patients treated in the same therapy group. In the NESS trial on group body psychotherapy [10], the ICC for therapy groups of 10 patients varied for different outcomes, but did not exceed 0.01 (which applied to the primary outcome). We assumed, conservatively, an ICC of 0.1. We assume a drop-out rate of 15% by the end of the study, so that if we allocate 10 patients on average to each therapy group we will end up with clusters with 8.5 patients on average. Assuming a coefficient of variation of cluster size of 0.5, we will need 200 patients before drop-out in 20 clusters in each arm to achieve 90% power at the 5% significance level [41]. Allowing, conservatively, for the additional loss of one full cluster in each arm, we plan to recruit a total of 2 × 210 patients.

The estimated loss takes into account drop-outs at each of the different phases of the study, i.e. between consent and beginning treatment, during treatment, during the 6-month follow-up period and during the 12-month follow-up period. Some patients will have to wait between giving consent and beginning of treatment. Within this period, they may drop out due to changing their mind, being offered alternative treatment or experiencing a reduction in symptoms. Based on previous studies [9, 10], we expect this drop-out rate to be less than 10% and we will be able to compensate for most of that loss through recruiting additional patients closely before the time of the baseline assessment.

During the treatment phase, we may have drop-outs from both groups. An intention-to-treat approach to analysis does not mean that all outcome data must have been collected, but it does mean that every effort should be made to minimise the amount of missing data. We expect a low drop-out rate from research during treatment but envisage a drop-out rate of 10% by the 6-month follow-up (in NESS [10] it was 7.3% after 6 months), and 15% by the 12-month follow-up.

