**Method**

The process evaluation will employ an embedded mixed methods design and will consist of data collection of video data of the intervention itself (through treatment fidelity analysis), client self-reported measures (weeks 2, 7, 12, 17 PHQ9, FE-GES, ORS) and qualitative end interviews scheduled within 6 months of the end of the intervention with participants and arts therapists. The interview is optional for participants but we aim to conduct a minimum of 45 interviews.

Quantitative analysis will provide a descriptive analysis of the course of process measures. We will descriptively explore whether there are any differences between compliant and non-compliant attenders, responders and non-responders and whether any socio-demographic and clinical characteristics are associated with outcomes.

Qualitative evaluation will comprise of one-off end-of-study interviews with participants from all 3 arts therapies modalities and control groups within 6 months of the intervention ending (weeks 20–48).

Participants will be purposively sampled so that we have a range of characteristics based on the following: treatment completers (attended > 75% of sessions) and partial-attendance (attended 35–75% of sessions), representation of each of the diagnostic groups (ICD10 F2, F3, F4), representation of a range of ages, each mode of therapy and sites. We aim to conduct interviews with up to 3 patients per arts therapies group and up to 10 control group participants, with an anticipated sample size of around 55 participants.

Interviews will last up to 1 h and will be conducted by an unblinded member of the research team. We will use an amended version of the Client Change Interview [36], which explores experiences of therapy, changes over a given time period and attributions for this. The amended version used in existing music therapy studies also explores participants’ experiences of the research process and involvement in the study as a whole. This information will provide understanding not only of the interventions but of how best to involve this patient group in trials in the future. Following advice from our LEAP, we will also interview the arts therapists providing the intervention as a means of triangulating patients’ experiences of change and relating identified changes to observations within the sessions. These interviews will also last for 1 h and will happen within 6 months of the therapy group ending.

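### Repeating the analysis within each diagnostic subgroup gives no test of whether the effect differs by diagnosis; an interaction is specified only for modality

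*Protocol article*

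**What the plan says.** Under Subgroup analyses (Methods for additional analyses {20b}), the protocol article sets two methods in one sentence. For diagnosis: "We will repeat analyses within diagnostic subgroups". For form of arts therapy, the question of different effects is addressed "by including an interaction between modality preference stratum and intervention vs. control in our mixed regression model".

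Objectives {7} lists, as a secondary objective, exploring the impact of "diagnosis and type of arts therapy upon outcomes in sub-group analyses". The eligibility criteria define three diagnostic groups: ICD-10 F2, F3 and F4.

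In the primary outcome analysis diagnosis is only an adjusting fixed effect, in the list "primary diagnosis, age, sex and baseline psychological distress". No intervention-by-diagnosis term appears anywhere in the article. Sequence generation {16a} balances primary diagnosis across therapy groups, so a typical group will mix diagnoses.

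**The concern.** A model fitted within one diagnosis estimates that diagnosis's effect and tests it against zero. Three such fits give three tests against zero and none of F2 against F3 against F4. Whether diagnosis changes the effect is a question about differences, and the stated method does not address it formally. For modality, the same sentence uses the method that does.

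The background section criticises trials restricted to one disorder, and the discussion presents this as the first trial to account for diagnostic heterogeneity in group arts therapies. Readers will therefore look at the diagnosis results with interest. If they see a significant effect in one diagnosis and not in another, with no test of the difference beside it, they may take the pattern as evidence that the therapy suits some diagnoses only. Subgroups of this size can easily produce that pattern when the effect is the same in all of them.

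**Working it through.** **Inputs from Sample size {14}.** Effect 0.5 SD ("We have designed the trial to detect a treatment effect of 0.5 standard deviations on the primary health outcome"); SD 0.81 ("the mean GSI was 1.65 with a standard deviation of 0.81"), so 0.5 × 0.81 = 0.405 GSI points; "We assumed, conservatively, an ICC of 0.1"; coefficient of variation of cluster size 0.5; 15% drop-out; 8.5 analysed patients per therapy group; 90% power at 5% (taken as two-sided); 200 per arm in 20 clusters, raised to 210 per arm.

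**The plan's own figure.**
- Individually randomised n per arm: 2 × (1.96 + 1.2816)² / 0.5² = 84.1, rounded up to 85.
- Design effect: 1 + ((1 + 0.5²) × 8.5 − 1) × 0.1 = 1.9625.
- Analysed per arm: 85 × 1.9625 = 166.8. Before drop-out: 166.8 / 0.85 = 196.3, rounded up to 197, or 20 clusters of 10 = 200. The stated figure is reproduced.

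**Power within one diagnosis.** Planned recruitment leaves 210 × 0.85 = 178.5 analysed per arm (21 groups of 8.5). The article gives no diagnosis shares, so they are assumed. For a share of one third:
- n = 178.5 / 3 = 59.5 per arm; patients of that diagnosis per therapy group = 8.5 / 3 = 2.83.
- Design effect: 1 + (1.25 × 2.83 − 1) × 0.1 = 1.254.
- SE = √(2 × 1.254 / 59.5) = 0.205 SD.
- Power = Φ(0.5 / 0.205 − 1.96) = 0.68.

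**Chance of a mixed pattern when every diagnosis has the same 0.5 SD effect.** This is 1 − P(all three significant) − P(none significant), with subgroups treated as independent.

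| Assumed shares | Power in each | All | None | Mixed |
|---|---|---|---|---|
| Equal thirds | 0.68, 0.68, 0.68 | 0.318 | 0.032 | 0.65 |
| 50/30/20 | 0.80, 0.65, 0.52 | 0.268 | 0.034 | 0.70 |
| 60/25/15 | 0.84, 0.59, 0.43 | 0.212 | 0.038 | 0.75 |

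**How far this moves.**
- No effect in any diagnosis: 1 − 0.95³ − 0.05³ = 0.14.
- Common effect 0.15 SD: about 0.3 without covariate gain, up to 0.4 if covariates explain 40% of the variance (assumed). At 0.25 SD: 0.52 to 0.68 over the same range. At 0.35 SD without covariate gain: 0.72. The figure is thus not monotone in the effect.
- At 0.5 SD, covariates explaining 25-40% of the variance (assumed): 0.31 to 0.64, depending on shares.
- At 0.5 SD, ICC 0.01 and 5% loss (assumed), equal thirds: n = 210 × 0.95 / 3 = 66.5; design effect 1 + (1.25 × 3.17 − 1) × 0.01 = 1.03; SE = 0.176; power 0.81; mixed 0.46. If covariates also explain 30% (assumed): power 0.92, mixed 0.21.
- Diagnoses share therapy groups, so subgroup estimates are correlated. If the group effect is common to all diagnoses (assumed), the correlation is (1.25 × 0.1 / 21) / (1.254 / 59.5) = 0.28. Simulation with equal thirds then gives a mixed pattern of about 0.54 at 0.5 SD.

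**The interaction test.** In 200,000 simulated trials per setting with a common effect of 0, 0.25 or 0.5 SD, a 2-df heterogeneity test rejected in 5% each time. Its power is limited. For two equal-third subgroups treated as independent, the SE of the difference is √2 × 0.205 = 0.290. Power for a 0.5 SD difference is Φ(0.5 / 0.290 − 1.96) = 0.41, and the difference detectable with 80% power is 2.80 × 0.290 = 0.81 SD. If the group effect is common to all diagnoses, one joint model removes it from the contrast: SE = 0.290 × √(1 − 0.28) = 0.246, and power rises to about 0.53.

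**The case against.** The strongest reply is that the article proposes no misuse. The objective is exploratory, and subgroup estimates with confidence intervals are a legitimate descriptive output. A detailed statistical analysis plan is to be signed off before unblinded analysis and may contain the interaction. The primary objective is tested on the whole sample and does not depend on the subgroups. The interaction test is itself weak.

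Much of this stands, and it limits the point. A reader might infer that differences by diagnosis are to be judged by comparing subgroup p-values. The article does not say so, nor that any difference will be declared from them. A reader might also infer that the method will usually produce a false contrast. That depends on the true effect, the diagnosis shares, the ICC and the covariate gain: the range above runs from 14% to about 75%, and every figure needs someone to compare significance across subgroups. A third tempting reading is that about three patients per group makes the cluster variance unusable in each fit. No calculation supports that, and about 42 therapy groups would remain.

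What does not stand is that this is merely detail left to a later plan. The article names a method for diagnosis, and separate fits do not become a test of difference by being exploratory. Low power for the interaction calls for intervals and caution; it does not favour separate tests.

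**Conclusion.** The point holds in a limited form. As written, diagnosis is handled by separate analyses that give no test of whether the effect differs between F2, F3 and F4. The question is a stated secondary objective, and the right tool is specified for modality in the same sentence.

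The 65-75% figure describes the risk if significance is compared across subgroups at the design effect. It rests on assumed shares, independent subgroups and no covariate gain. It should be quoted with those conditions and beside the interaction test's 5%. It does not predict what the trial team will do, and the primary analysis is unaffected.

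**What to change.** In the statistical analysis plan, before unblinded data are analysed:

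- Add a diagnosis-by-intervention interaction (2 df) to the mixed model already planned, as is done for modality preference.
- Report the effect in each diagnosis, with a 95% confidence interval, as a contrast from that model.
- Rest any claim that the effect differs by diagnosis on the interaction test alone.
- Label the analysis exploratory and state its low power: about 41% for a 0.5 SD difference between two equal-third subgroups.

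The cost is a few lines of text. Diagnosis is already collected, balanced at randomisation and in the model, so no data, visits or patients are added. If the unseen plan already contains this term, it need only be confirmed.
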